**8.3 STUDY OUTCOMES**

**8.3.1 Primary Outcome**

1. INPREP Pathway adherence: rate of patients who received NPWT (according to eligibility and duration of application defined within the INPREP Pathway)

**8.3.2 Secondary Outcomes**

***Secondary Implementation Outcomes:***

1. *Appropriateness* – clinician and patient carer perspective of pathway and procedure, Intervention Appropriateness Measure (39), CFIR observation/field notes
2. *Acceptability* clinician and patient carer perspective, Acceptability of Intervention Measure (39), and CFIR observation/field notes
3. *Feasibility* clinician and patient carer perspective, Feasibility of Intervention Measure (39), and CFIR observation/field notes

***Secondary Patient Outcomes:***

1. *Healing outcomes:* i) Time/days to re-epithelialisation (blinded photo assessment), ii) skin grafting requirements, iii) burn wound exudate, iv) number of dressing changes, v) adverse events (26).
2. *Operating theatre requirements:* i) proportion patients requiring an operation (%), ii) operations required per patient, iii) operative procedures performed (e.g., skin graft) (26).
3. *Hospital requirements 12 months post-injury:* i) proportion of patients needing ≥1 admissions to hospital (% & length of stay), ii) number of outpatient appointments, iii) number of scar clinic appointments.
4. *NPWT device malfunctions:* i) alarms ii) charging issues

***Secondary Resource use outcomes (12-month time horizon):***

1. Implementation costs (e.g., change facilitator, staff time for training, resources and materials).
2. Health care resource use for study interventions (e.g., time to apply NPWT, cost of device, other dressings used, procedures, unexpected return to hospital, time to remove and reapply NPWT at follow-up dressing change appointments)

**8.4 STUDY PROCEDURES**

Five steps will be sequentially rolled out across the 4 hospitals over 13 months: **1. Set up** ensures adequate training and collection of control and intervention data. **2. Control steps**-are usual care, i.e., standard silver dressings. **3.** **Intervention establishment** involves the research nurses (ReNs) collaborating with the NAG and local champions to promote the INPREP Pathway and delivering the companion implementation strategies. A project manager will develop a study manual and training schedule for ReNs, monitor data integrity, intervention fidelity log and collaborate with the team (ReNs and CIs) to promote intervention fidelity. **4. Implementation period** is intervention exposure. **5. Sustainability** of adherence measured. In both control and implementation steps other burn care will be as per local standards (40). Implementation education will provide evidence-based advice, but treating clinicians will determine definitive care (e.g., inpatient versus outpatient care) based on patient needs and healthcare priorities.

**Figure 2.** Steps for the multi-centre, prospective, pragmatic, stepped-wedged randomised controlled trial

[figure not shown]

**Figure 2**. Illustrates the five steps of the multi-centre, prospective, pragmatic, stepped-wedged randomised controlled trial that will be conducted across the four participating paediatric hospitals. Following initial set up, all participating sites will start the trial in control phase with the baseline measures taken, and then one site will randomly step up (computer-generated, centralised randomisation) to implementation every 6 weeks, until saturation of the implementation intervention across all sites.

**8.4.1 Recruitment of participants**

Wherever possible, prospective informed consent will be obtained from parents and caregivers (and the child where age appropriate) in the ED following initial patient presentation to hospital. We are requesting consent to continue (also referred to as deferred consent or research without prior consent) for Phase 2 of this investigation in extenuating circumstances where prospective informed consent is not possible, practical, or appropriate to obtain. As the intervention in this trial is accepted as current clinical practice, and carries no greater risk than standard care, deferred consent will be obtained in certain circumstances where approaching the parent/caregiver and child in the ED is considered to be inappropriate, and likely to increase parental and patient distress. In these circumstances where deferred consent is required, parents and caregivers will be informed about the research as soon as possible after it commences and their written consent for continuing involvement will be sought. Consent to continue (deferred consent) will be obtained from parents and caregivers within 24-hours following initial presentation to hospital for their child’s burn injuries. Consent will be obtained as close to 24-hours as possible but no later than 72-hours. Parents and caregivers, and the child where age appropriate, will be approached by a member of the research team and presented with information regarding the trial in the ED. Parents and caregivers will be given an opportunity to read through the PICFs in the ED and any questions they have will be answered. In cases where the emergency situation surrounding the child or young person is sufficiently distressing to the parent or carer, and it could be considered inappropriate to approach the parents acutely, verbal consent will be obtained via telephone within 24 hours after commencement of the research. Following verbal telephone consent, written consent for continuing involvement will be obtained at the child’s first dressing change in the Burns Outpatient department for paediatric outpatients, and within 24-hours for inpatients.

For paediatric patients and families not scheduled to return to the Burns Outpatient Department within 72 hours post-burn, written informed consent will be obtained using a REDCap link tick box – emailed to the parents and carers. It will be made clear that if the parent/caregiver withdraws at that point, or anytime thereafter, they will be given the option to have any collected data or samples destroyed. All communications between research staff and parents and caregivers will account for, and take into consideration, the stress and emotional factors associated with having an acutely burned child. Research staff will ensure that the dependency of potential participants and their patents and caregivers on ED and burns clinicians providing burn treatment will not influence their decision to participant in the research. Paediatric patients involved in this investigation may be critically ill, and unfortunately despite best efforts, some of the patients may die as a result of their burn injury before permission to use the collected data can be obtained. In these cases, data will be discarded and all biospecimen samples will be destroyed as per standard operating procedures for the destruction of biological samples at each partnering site.

**8.4.2 Data Collection**

Research Nurses (ReNs) will collect primary and secondary outcome data prospectively by a combination of observation of, clinical staff, and patients/carers and electronic medical records (EMRs), using methods from previous studies (14, 41). Patient demographic and clinical characteristics will be recorded at initial presentation to the ED or burns service via EMR. Wound photos will be taken with a study iPad at each dressing change and deidentified for blinded review to assess and establish time to healing. ReNs will collect hospital data interactions (such as outpatient appointments, planned or unplanned return to ED, operating theatre and admission requirements) from each patient for 12 months post injury. Where possible burn wound exudate will be collected at NPWT application and removal and will be analysed using previous techniques (31) and related to the healing outcomes, to identify biological and biochemical mechanisms (42). ReNs will capture site level measures (e.g., ratios of burns treatment complications). The schedule of assessments for the trial is presented in Appendix 5.

Data will be directly entered by ReNs into a REDCap database (Research Electronic Data Capture, Vanderbilt, USA, hosted at Griffith University) using password-protected iPads. Identifying information will only be stored at the site level. Patient questionnaires will be completed over the telephone by an alternative site ReN (who is blinded to the crossover schedules) at three months post burn injury. We will instruct patients not to disclose their allocation (control or INPREP) to the ReN. Staff web-based questionnaires will be sent out 4 weeks into implementation and at completion of implementation phase. ReNs will conduct CFIR-informed clinician observations, interviews, and document analysis at each participating site.

**8.4.3 Collection of Biospecimens**

Potential participants will be approached for biospecimen collection if it will be possible to collect a sample of their burn wound exudate, blood, or urine as part of their normal wound care procedures or standard care. As part of routine burn wound cleaning procedures, wound exudate or fluid is removed and usually discarded. Instead, for this study, it will be retained for analysis. If participants will be sedated or under a general anaesthetic (GA) for their standard wound care procedures, or require a cannula or routine blood draw at the time of their hospital visit, this will enable collection of blood, which will be retained for analysis. If participants are scheduled to receive a urinary catheter as part of routine standard treatment for their burns, this will enable the collection of urine that will be retained for analysis. For participants who do not require a catheter, the child and parent/caregiver will be asked if they consent to providing a urine sample and will be given a urine sample pot container. Whilst not collected as part of routine standard care for burn injuries, hair samples will also be collected from consenting patients and parents/caregivers. Additional information on biospecimen sampling is provided under section *8.4.4.2 Healing outcomes.*

- - 1. **Measurement tools used**
       1. Appropriateness, Acceptability, and Feasibility of the INPREP Pathway
- Appropriateness of the INPREP Pathway and procedures, from the perspective of the clinician and patient carer, will be assessed using the Intervention Appropriateness Measure (39) and CFIR observation and/or field notes
- Acceptability of the INPREP Pathway, from the perspective of the clinician and patient carer will be examined using the Acceptability of Intervention Measure (39) and CFIR observation and/or field notes
- Feasibility (from the clinician and patient carer perspective) of the INPREP Pathway will be assessed using the Feasibility of Intervention Measure (39) and CFIR observation/field notes
  - - 1. Healing outcomes
- Time to re-epithelialisation (days) will be examined using blinded photo assessment of patient’s injuries. Wounds will be photographed by the ReNs, using the study iPad, at each dressing change until the wound is considered 95% re-epithelialised by the child’s treating clinician at the site, and the wound no longer requires definitive silver dressings. A panel of burn experts (comprising of paediatric surgical consultants and experienced burns nurses) will perform a blinded review of patient’s photographed burn wounds – assessing if wounds are 95% re-epithelialised. Photos will be taken of patient’s burn injuries by the ReN at each follow up dressing change appointments This method has previously been used in recent trials assessing time to re-epithelialisation in paediatric burn patients (14, 41).
- Proportion of paediatric burn patients who require a skin graft for their injuries (rate of skin grafting), as well as adverse events (AE) and referrals to scar management will be documented in this investigation. The number, and type, of dressing changes until wound closure will also be recorded for all patients via observation and electronic medical record assessment.
- Biological molecules associated with healing (e.g., inflammatory markers, extracellular matrix production or remodelling, skin cell growth) will be assessed using wound exudate analysis. Any wound fluid able to be collected at NPWT application and removal will be analysed using previous techniques (31, 43) and related to the healing outcomes, to identify biological and biochemical mechanisms associated with wound healing or scarring (42).

*Wound Exudate Collection:*

Wound exudate will be collected from the participants during routine wound cleaning procedures. Instead of being discarded, the burn wound exudate will be retained and stored using the Standard Operating Procedure SOP-Wound-Fluid (see Appendix 1). Filter paper will be placed at the edge of the burn wound to absorb the wound exudate (44, 45). A comprehensive mass spectrometry (MS) analysis is possible from biological samples collected on paper (46). Researchers at the QCH site have previous experience collecting wound exudate from NPWT devices (43) and directly from the wound (47), and identifying proteins in these samples (31). Briefly, samples will be centrifuged to pellet cell debris and the supernatant will be aliquoted into tubes. Samples will be stored at -80C in a research facility or hospital laboratory at each site.

- Stress will be examined using a number of techniques in this investigation including hair, urine and blood, analysis where opportunistic sampling is possible – and when resources and ethics is available at partnering sites. The collection of blood and hair samples from paediatric burn patients will provide insight into the impact of the burn on a range of body systems – and how this impact might lead to prolonged wound healing and maladaptive outcomes in children with burn injuries. See Appendix 2 and 3 for additional methods and procedures for patient blood and hair sampling.

*Blood Collection:*

Using an opportunistic sampling method, blood will be collected from the participants during routine wound care procedures. In cases where the participant is scheduled to receive a routine blood draw, canula insertion, or is receiving a GA for routine burn treatment – blood will be collected, processed and stored using SOP-Blood-Processing (see Appendix 2). Briefly, blood will initially be collected in a heparinised tube. A small amount of whole blood will be removed and prepared for transcriptomic (gene expression), epigenetic and immune phenotypic assays. The remaining sample will be processed through several centrifugation steps, and Peripheral Blood Mononuclear Cells (PBMCs) and plasma will be isolated. The plasma, whole blood isolates and cells will be aliquoted into tubes. Plasma and whole blood samples will be stored at -80^◦^C and cells will be stored in liquid Nitrogen in a research facility or hospital laboratory at each site. No more than 5% of the whole blood volume will be removed in a single occasion. In cases where paediatric patients do not require blood sampling, canulisation, or a GA as part of their routine standard care – blood collection will not be performed. All patients will be offered a numbing cream to help reduce pain during blood sampling if there are concerns regarding discomfort.

*Hair Collection:*

A hair sample containing approximately 100 strands of hair and a minimum of 3cm in length will be collected from the area at the nape of the neck, cut as close to the scalp as possible using scissors (see Appendix 3). Patient’s hair characteristics (e.g. colour, washing episodes per week, and presence of hair dye or product) will also be recorded from parents and caregivers, and the child where age appropriate.

*Urine Collection:*

Where possible, urine will be collected from the participants. If participants are scheduled to receive a urinary catheter as part of routine standard treatment for their burns, some urine that will be retained for analysis (see Appendix 4). For participants who do not require a catheter, the child and parent/caregiver will be asked if they consent to providing a urine sample and will be given a urine sample pot container for collection. A minimum volume of 60mL is required for analysis. The sample will be immediately frozen at -20^◦^C to prevent microbial contamination or proteolytic degradation. The next day or later, the sample will be clarified by centrifugation, filtered to remove bacteria or protein aggregates, and concentrated using previously established techniques (48) and then stored at -80^◦^C in aliquots for analysis.

- - - 1. Operating theatre requirements
- Proportion (%) of patients requiring an operation, in addition to the number of operations required per patient, and the type of operative procedures performed (e.g., skin graft) will be recorded via observation and electronic medical record assessment
  - - 1. Hospital requirements 12 months post-injury
- Rate of patients needing ≥1 admissions to hospital (% and length of stay), as well as number of outpatient appointments and number of scar clinic appointments will be recorded via observation and electronic medical record assessment
  - - 1. Healthcare resource use for study interventions

Healthcare resource use will be calculated using variables such as time to apply NPWT, cost of device, other dressings, procedures, and unexpected return to hospital. This data will be captured via observation and review of electronic medical records

- - - 1. Implementation costs

Healthcare resource use will be calculated using variables including change facilitator, staff time for training, resources, and materials.

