**2.2 Negative pressure wound therapy**

There is now strong evidence through experimental (16, 25, 26) and prospective cohort studies (15, 17, 27-29) that support the benefits of NPWT in acute burn care. Compared to standard silver dressings alone, adjunctive NPWT improves time to healing and decreases dressing change requirements and referrals for scar management. Negative pressure wound therapy (NPWT) offers a cost-effective solution for the treatment of paediatric burns. A recent study by our team evaluating the healthcare costs of NPWT in small-area paediatric burns found the mean total cost per person for the standard silver dressings group was $1,669.01 (95% CI 659.06 to 3269.16), compared to $903.69 (95% CI 670.68 to 1234.74) for the NPWT group (13).

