**12.2 Statistical analysis methods**

Generalised Linear Mixed Models (fitting a random intercept to account for clustering, random effect) and Generalised Estimating Equations (using the individual as the clustering unit) will be used to compare the effect of switching from the usual care to INPREP condition on primary and secondary outcomes. Specifically, an appropriate protocol for model selection based on Zuur *et al*. (2009) will be applied (49). This analysis approach is able to account for potential temporal trends, using time as a covariate, in addition to clinical explanatory variables (total body surface area, age, gender), which will be included in each model. It should be noted that other covariates, such as time, could be used as random effects in the mixed models.

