**Appendix 5. Schedule of Assessments**

| Visit | Initial Presentation | COD1 | COD2, COD3…^1^ | Surgical intervention | 3 months | 12 months |
| --- | --- | --- | --- | --- | --- | --- |
| Eligibility and consent |  |  |  |  |  |  |
| Eligibility screen | X |  |  |  |  |  |
| Signed informed consent | X |  |  |  |  |  |
| REDCap data collection forms |  |  |  |  |  |  |
| Demographic and Injury Details | X |  |  |  |  |  |
| Initial Presentation | X |  |  |  |  |  |
| First Change of Dressing |  | X |  |  |  |  |
| Ongoing Dressing Changes |  |  | X |  |  |  |
| Surgical Interventions & Requirements |  |  |  | X |  |  |
| Completion Data |  |  |  |  |  | X |
| Additional data points |  |  |  |  |  |  |
| Time taken to complete dressing | X | X |  |  |  |  |
| % Re-epithelialised | X | X | X | X |  |  |
| Burn depth re-assessment |  | X |  |  |  |  |
| Photos^2^ | X | X | X | X |  |  |
| Pain scales |  |  |  |  |  |  |
| Clinician pain scales – FLACC/NRS^3^ |  |  |  |  |  |  |
| Baseline | X | X | X | X |  |  |
| Peak procedural | X | X | X |  |  |  |
| Parent-proxy pain scales - NRS |  |  |  |  |  |  |
| Baseline | X | X | X | X |  |  |
| Peak procedural | X | X | X |  |  |  |
| Patient pain scales – FACES^4^ |  |  |  |  |  |  |
| Baseline | X | X | X | X |  |  |
| Peak procedural | X | X | X |  |  |  |
| Implementation outcomes^5^ |  |  |  |  |  |  |
| Clinician | X | X |  |  |  |  |
| Parent-Guardian |  | X |  |  |  |  |
| Biological Samples |  |  |  |  |  |  |
| Urine Sample | X | X |  |  |  |  |
| Blood Sample^6^ | X | X | X | X |  |  |
| Wound Fluid | X | X^7^ |  |  |  |  |
| Hair Sample | X |  |  |  | X |  |

COD = change of dressing; FLACC = face, legs, activity, cry, consolability; NRS = numeric rating scale; FACES = faces pain scale – revised

^1^ Every change of dressing until patient is 95% re-epithelialised.

^2^ Wound photos to be taken after debridement but before dressing application.

^3^ FLACC to be collected if patient under 7 years of age, NRS to be collected if patient ages 7 or over.

^4^ Patient pain scales only required for patients aged 7 years or older.

^5^ Implementation outcomes only required for patients enrolled in the intervention arm.

^6^ Only if patient is already cannulated or undergoing procedure under a general anaesthetic.

^7^ Only if patient in intervention arm and wound fluid able to be collected from NPWT device tubing.

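### Time to re-epithelialisation is read blind, but an open-label site clinician ends the photographs, and wounds the panel does not confirm have no event date

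*Protocol*

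**What the plan says.** Section 8.3.2 of the protocol lists time to re-epithelialisation, assessed from photographs by blinded review, first among the healing outcomes. Section 8.4.2 has the photographs "deidentified for blinded review to assess and establish time to healing".

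The healing-outcomes text (8.4.4.2 by the protocol's own cross-reference) says that the expert panel "will perform a blinded review of patient’s photographed burn wounds – assessing if wounds are 95% re-epithelialised". The same text sets when photography ends. Whenever the dressing is changed, a research nurse photographs the wound, "until the wound is considered 95% re-epithelialised by the child’s treating clinician at the site". A second condition is joined to that one: "and the wound no longer requires definitive silver dressings". Appendix 5, footnote 1, gives a shorter rule: "Every change of dressing until patient is 95% re-epithelialised".

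For analysis, section 12.2 names generalised linear mixed models and generalised estimating equations, which "will be used to compare the effect of switching from the usual care to INPREP condition on primary and secondary outcomes". It adds time, total body surface area, age and gender as covariates and leaves model selection to a cited text. It does not mention event times, censoring or grafting.

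**The concern.** The blinded panel is there to keep knowledge of the condition out of the healing date. The stopping rule lets some of it back in. The protocol does not call the treating clinician unblinded in so many words, but this follows from the design: the pathway is implemented site by site, with training and local promotion.

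Once that clinician has made the call, no later image exists. The panel can move the date earlier but not later. If it finds the last photograph below 95%, the protocol does not say whether the child counts as healed on that day, is censored or is dropped.

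Healing is also seen only at dressing changes, so each date is known only to lie between two visits. A grafted wound does not reach the endpoint unaided, and section 5.2 expects surgery to differ between the phases. Section 5.2 also predicts faster healing, so this outcome carries the first part of the secondary hypothesis.

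**Working it through.** **No figure to reproduce.** The protocol gives no sample size, median, spread or censoring rate for healing time. Its only power statement (section 12.1) concerns adherence.

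**Step 1: what the panel can observe.** Let P be the dressing change at which a blinded panel would first accept 95%, and C the one at which the clinician's call ends photography.
- P ≤ C: the panel dates healing at P.
- P > C: there is no photograph at P, so no panel date exists.

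The two-part rule in the healing-outcomes text can push C later than the 95% call alone, because silver dressings must also have ended. Both parts are still judged at the site.

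**Step 2: what this could do.** Illustration by simulation, 200,000 children per condition. All inputs are assumed except the 22% benefit (ratio 1 − 0.22 = 0.78), which section 2 reports from the earlier randomised trial at one of the sites:
- log-normal healing time, control median 10 days, log-SD 0.5;
- dressing changes every 3, 5 or 7 days, equal in both conditions;
- clinician reading error 0.10 on the log scale, panel always correct;
- where the panel does not confirm, the last photograph is counted as healed.

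Entries are ratios of geometric mean days, INPREP over control.

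| Who ends photography, and when | True ratio 1.00 | True ratio 0.78 |
| --- | --- | --- |
| Panel itself confirms 95% | 1.00 | 0.81-0.83 |
| Clinician, same behaviour in both conditions | 1.00 | 0.83 (7-day spacing) |
| Clinician about 10% earlier under INPREP | 0.94-0.95 | 0.77-0.79 |
| Clinician about 20% earlier under INPREP | 0.87-0.88 | 0.71-0.74 |
| Clinician about 10% later under INPREP | 1.02-1.03 | 0.84-0.85 (5- and 7-day spacing) |

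Wounds without a panel-confirmed date: 6-14% with unbiased clinicians, 17-35% where they call healing about 10% early. Dropping those children does not help: under a true ratio of 1.00 it gives 0.92-0.96 for the 10% earlier call and 0.81-0.90 for the 20% earlier call.

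**Step 3: visit spacing.** Taking the visit date as the healing date adds about half the gap g between visits, so mean delay ≈ g/2. Equal spacing keeps a true 1.00 at 1.00 but pulls a true 0.78 to 0.81-0.83 (first row). If gaps differed, say 3 days in control and 5 or 7 under NPWT (assumed), the artefact would be (5 − 3)/2 = 1 day or (7 − 3)/2 = 2 days. A true 1.00 would then read 1.09 or 1.16, and a true 0.78 would read 0.89 or 0.96. That direction hides benefit.

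**The case against.** The strongest reply is that the outcome is blinded where it matters: images are de-identified and an expert panel reads them. This stands. A reader might infer that the endpoint is not blinded at all, but the documents do not support that. Only the end of observation depends on the site.

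Second, section 12.2 does not rule out a proper event-time analysis. A binomial mixed model on healed or not healed at each visit is a discrete-time hazard model, which handles grouped times and right-censoring. Such detail is commonly left to a statistical analysis plan, which is not shown here. This also stands, so it cannot be said that the named models ignore censoring. It does not cover the stopping rule, because no analysis plan can recover photographs that were never taken.

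Third, a reader might infer that healing time will be wrongly estimated, or set the 1-2 day spacing artefact against 22% of an assumed 10 days (0.22 × 10 = 2.2 days) and conclude that much of the expected effect is at stake. The documents do not support this either. With equal clinician behaviour and equal spacing, a true ratio of 1.00 stays at 1.00. The only text on spacing, in section 2.2, is that NPWT "decreases dressing change requirements". That concerns the number of changes, which falls with faster healing alone: at 3-day visits, healing at day 10 takes 4 changes and at day 7.8 (10 × 0.78) takes 3.

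**Conclusion.** The point holds in a limited form. The stopping rule lets an open-label judgement set the latest date the blinded panel can give, and it leaves unconfirmed wounds without an event date. The analysis section gives this outcome no event-time structure, although the family and data layout it leaves open could supply one.

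Bias needs a clinician's call or a visit schedule that differs by condition. The protocol does not show either, so size and direction cannot be derived from it. The ratios above show only how the mechanism works under assumed healing times, visit gaps and call shifts. The loss of panel-confirmed dates needs no such difference, although its share (6-14% with unbiased clinicians) also rests on those inputs.

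This concerns a secondary outcome. Adherence, the primary outcome, is unaffected. The change is worth making because it is cheap and part of it must be in place before the photographs are taken.

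**What to change.** **Data collection (healing-outcomes text and Appendix 5).** Take one more photograph at the next routine visit after the clinician's call, where such a visit occurs. State that the panel's reading, not the clinician's call, defines the event. Bring footnote 1 of Appendix 5 into line with the two-part rule in the text.

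**Analysis (section 12.2 or the analysis plan).** Treat healing as time to event. The lower bound is the last photograph the panel judged below 95%; the upper bound is the first it judged at or above 95%. Fit an interval-censored or discrete-time hazard model with site and period effects. Right-censor at the last photograph if the panel never confirms, and treat grafting as a competing event. Report unconfirmed wounds by condition: they leave view when close to healing, so censoring alone does not remove a bias from a differential call, and the extra photograph matters more.

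**Covariate.** Add initial burn depth to total body surface area, age and gender in the healing and grafting models. Appendix 5 lists a depth re-assessment at the first dressing change, which implies an initial one. Use the initial value only, since the later one follows treatment.

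**Cost.** A slightly more complex model and a few extra photographs at visits that take place anyway. Children with no later visit gain no extra photograph, so some unconfirmed wounds will remain.
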